## Abstract

**Background:**

Children with severe acute malnutrition (SAM) have a high risk of mortality and morbidity. After recovery from an initial episode of SAM, the risk of relapse can be high, although estimates vary across settings. Post-recovery surveillance for relapsed SAM in Burkina Faso consists of monthly clinic-based follow-up visits. However, adherence to the follow-up schedule can be variable, and children with missed surveillance visits may have delayed diagnoses of relapse. Here, we describe the protocol for a feasibility trial design to provide preliminary evidence to support the training of caregivers to screen for relapsed acute malnutrition using mid-upper arm circumference (MUAC) screening at home.

**Methods:**

This feasibility trial will enroll 200 caregiver-child dyads in which the child has recovered in the past month from an episode of SAM in Boromo, Burkina Faso. Eligible children had an initial episode of SAM that they recovered from per Burkinabè guidelines (weight-for-height *Z*-score, WHZ ≥ −2 and/or MUAC ≥ 12.5 cm, depending on the admission criteria). Caregiver-child dyads are randomized to either weekly screening using a standard MUAC tape plus standard of care follow-up or standard of care alone, which consists of monthly clinic-based screening for relapse for 3 months. Caregiver-child dyads are followed for 6 months. Primary feasibility endpoints include acceptability, time for training, enrollment potential and refusals, adherence to the follow-up protocol, and adherence to the screening protocol. Clinical endpoints, measured to inform the design of a full-scale trial, include the proportion of children relapsing, anthropometric measurements at 6 months, hospitalization, and vital status.

**Discussion:**

This feasibility trial will generate data to support the development and full-scale testing of an intervention to train caregivers to screen for relapsed acute malnutrition using MUAC.

**Trial registration:**

This trial is registered at clinicaltrials.gov (NCT05932992), first posted 27 June 2023.

## Background

Severe acute malnutrition (SAM) affects 19 million children every year, most of whom are in sub-Saharan Africa and South Asia [1]. SAM is defined as a mid-upper arm circumference (MUAC) of < 11.5 cm and/or weight-for-height *Z*-score (WHZ) < −3 among children aged 6 to 59 months. Uncomplicated SAM is treated on an outpatient basis, with children receiving a package of interventions including ready-to-use therapeutic food (RUTF), antibiotics, antiparasitics, and any missing vaccinations [2]. The major goal of these programs is to induce rapid, acute weight gain in children to improve the probability of survival during the acute episode. Children are followed weekly until nutritional recovery, typically for several weeks to months. While specific criteria for achieving recovery vary by country and context, children are typically considered to have recovered if they have met specific anthropometric thresholds, typically MUAC ≥ 12.5 cm and/or WHZ ≥ −2 with no edema, and the child has been in treatment for at least 4 weeks. Most interventions for SAM focus on improving the probability of nutritional recovery.

Relapse after recovery from SAM has been increasingly recognized as a contributor to poor outcomes. Evidence suggests a large degree of variation in the proportion of children who relapse after successful SAM treatment, with as many as 37% of successfully treated children relapsing up to 18 months after treatment [3]. Children with SAM with worse anthropometric deficits at program admission have worse outcomes compared to those with better anthropometric deficits [4]. Children who relapse with SAM are re-admitted to nutritional programs. Identifying children who have relapsed earlier may improve outcomes in these children.

Studies have previously shown that caregivers can be trained to detect acute malnutrition using MUAC measurements as well as community health workers [5]. In addition, the feasibility of caregivers screening for MUAC and danger signs of SAM has been demonstrated among children actively enrolled in outpatient nutritional programs for SAM [6]. However, a trial comparing a reduced follow-up schedule after admission to the program plus at-home surveillance using MUAC and training in clinical danger signs found lower nutritional recovery in the reduced follow-up schedule arm compared to the standard of care (weekly follow-up) arm [7]. In Burkina Faso, standard of care for follow-up following recovery from SAM includes monthly clinic visits for 3 months following program discharge. Burkina Faso has a high prevalence of SAM, with more than 100,000 cases among children under 5 years of age each year [8]. Here, we describe the protocol for a randomized controlled trial designed to evaluate the feasibility and acceptability of training caregivers to screen children who have recovered from SAM weekly for signs of acute malnutrition using a standard MUAC tape.

## Methods/design

### Aims and hypotheses

The overall objectives of this trial are to establish the feasibility of training caregivers to screen for relapse using standard MUAC tapes among children who have recovered from SAM. In addition, we aim to determine the burden of post-discharge relapse following recovery from an episode of SAM, to inform the design and feasibility of a full-scale trial of caregiver screening for the detection of relapse. We hypothesize that caregivers will find MUAC screening feasible and acceptable as demonstrated by the time for training, willingness to participate in training, enrollment, and follow-up in the trial, and accuracy of caregiver measurements.

### Ethics

The study was reviewed and approved by the Institutional Review Board at the University of California, San Francisco (Protocol 23–38829) and the Comite d’Ethique pour la Recherche en Santé in Ouagadougou, Burkina Faso (Protocol 2023-09-219). Written informed consent is obtained from the caregiver for both their participation and the participation of their child.

### Study design

This study is a 1:1 randomized feasibility trial in which caregivers of children who recovered from SAM in the past month are randomized to either training in weekly at-home screening using a standard MUAC tape for detection of relapsed SAM or standard of care, which includes monthly, clinic-based follow-up. Caregiver-child dyads are followed for 6 months from enrollment to assess feasibility, acceptability, accuracy, and anthropometric and other clinical endpoints.

### Setting

This study is being conducted in Boromo, Burkina Faso. Boromo district is in central Burkina Faso. This district experiences a large burden of SAM annually. This study is being implemented in 10 Centres de Santé et de Promotion Sociale (CSPS) which treat approximately 500 cases of SAM annually. CSPSs provide outpatient primary treatment, preventative care, and antenatal and maternity care, and host outpatient nutritional programs once a week in which they screen and provide care for uncomplicated SAM.

### Recruitment and eligibility criteria

Caregiver-child dyads are recruited based on nutritional program registers which record outcomes for all children who are treated as part of the outpatient nutritional program. Caregivers of children who have received outpatient treatment for SAM and who have recovered from their SAM episode are screened by a study nurse for eligibility in the present trial. Caregiver-child dyads are eligible to participate if the caregiver is at least 18 years of age, the child is between 6 and 59 months, the child has recovered from an episode of SAM per Burkinabè national guidelines (MUAC ≥ 12.5 cm and/or WHZ ≥ − 2, depending on which criterion the child was admitted to the nutritional program) in the past month, the family is planning to stay in the study area for 6 months to facilitate retention in the study, and with appropriate consent from the caregiver or guardian.

### Randomization and masking

Caregiver-child dyads are randomized on a 1:1 basis without stratification or blocking. Given the nature of the intervention, investigators, participants, and caregivers are not masked to their assigned treatment. To minimize contamination, each caregiver was given only a single MUAC tape for measuring their child, and multiple children from the same family were not enrolled. Nutrition program staff who evaluate children returning to the clinic for relapse are masked to the intervention assignment.

### Interventions

Caregivers who are randomized to the MUAC screening arm are trained by a study team member after enrollment in the trial. Each caregiver who is randomized to MUAC screening is given a standard color-coded MUAC tape. Caregivers receive a brief training in how to use and interpret the MUAC tape. Caregivers are instructed to measure the child’s MUAC weekly for 6 months and to return to the CSPS with their child for care if their child’s MUAC measurement is red (SAM, MUAC < 11.5 cm). In the standard of care arm, caregivers are instructed to bring their child in monthly for screening and nutritional counseling for three months, per Burkinabè national guidelines. Regardless of their anthropometric measurements, children who have recovered from SAM are enrolled in a moderate acute malnutrition (MAM) care program for three months. Children in the caregiver screening arm will also receive all the care packages provided in the standard of care. One study nurse per facility (*N* = 10 total) is responsible for implementing the intervention. Each nurse completed a 2-day didactic and practical training on study procedures prior to the start of the study. Intervention fidelity is ensured via regular supervisory visits from study investigators and supervisors to ensure the study protocol is followed.

### Participant timeline, procedures, and follow-up

After enrollment, participants are followed monthly for 6 months. Per Burkinabè guidelines, caregivers are requested to bring their children back monthly for acute malnutrition screening and nutritional counseling. To understand adherence to the follow-up schedule, no efforts beyond those routinely implemented by the nutritional program to follow up children are employed. The primary endpoint of the trial is 6 months after enrollment (Fig. 1). While caregivers are requested to bring their child back to the clinic for this follow-up visit, phone calls to find the family and home visits are used in case the caregiver does not return to the clinic. At each study visit, anthropometric measurements are collected, including weight using a standing scale (Seca GmBH, Germany), height using a ShorrBoard (Weigh and Measure, LLC, Maryland, USA), and MUAC using a standard MUAC tape. At each follow-up visit, caregivers are asked about any care they sought for their child, reasons for seeking healthcare, and hospitalization.

**Fig. 1 Fig1:**
[figure not shown]
Participant flow diagram for the trial. Abbreviations: CSPS, Centre de Santé et de Promotion Sociale; SAM, severe acute malnutrition; WHZ, weight-for-height *Z*-score; MUAC, mid-upper arm circumference; SOC, standard of care

### Feasibility and acceptability outcomes

The primary outcomes for the trial are focused on feasibility and acceptability. Feasibility endpoints focus on both the feasibility of conducting a large-scale trial that is powered for relevant clinical outcomes as well as feasibility of integration of caregiver screening into the existing health system. Acceptability focuses on acceptability of integration of caregiver screening from both the caregiver and clinic perspective.*Enrollment and follow-up*. We will assess the speed of enrollment and rate of refusal to enroll in the trial as an indicator of potential for enrollment in a full-scale trial. We will consider success to be enrollment of the target sample size in a 6-month period and refusal of < 10% of eligible participants. We will also assess follow-up at the 6-month primary endpoint visit and consider success to be retention of > 85% of participants at 6 months.Proportion of children who relapse. Assessment of the proportion of children who relapse over the 6-month period post-discharge will establish how frequently children relapse in this population, which will contribute to sample size calculations and justification for a full-scale trial. A low probability of relapse would indicate that interventions intended to reduce the risk of relapse are not warranted.Time to conduct MUAC training. To understand the additional burden on the existing healthcare system for training caregivers to screen for MUAC, the time training takes for each caregiver is measured during the enrollment visit. Extended time for training would be more difficult to implement in real-world nutritional programs. An acceptable time for training will be established via nutrition program interviews as part of the acceptability assessment, described below.*Accuracy of caregiver MUAC training*. At enrollment and 6 months, the accuracy of caregiver MUAC measurements against a gold standard (nutrition program staff) measure is collected. The caregiver and the nutrition program staff member each measure the MUAC of a child attending the clinic masked to each other’s measurements, categorized as “normal” (≥ 12.5 cm, green section of tape), “moderate acute malnutrition” (< 12.5 cm to ≥ 11.5 cm, yellow section of tape), or “severe acute malnutrition” (< 11.5 cm, red section of tape). Due to high levels of caregiver illiteracy, we will not collect numeric measurements. Concordance between color-based categories will be assessed to measure accuracy.*Adherence to the intervention*. Caregivers in the MUAC screening arm will be asked to report how often they screened their child at each follow-up visit. Infrequent caregiver screening would indicate that the intervention may not be acceptable or feasible. Caregivers are also asked to bring back the MUAC tapes at each visit, so the study team can confirm that they are still in possession of the caregiver and ensure that they are not damaged. Missing or damaged MUAC tapes are replaced and recorded.*Adherence to the follow-up schedule*. Standard of care in Burkina Faso includes monthly follow-up visits in the clinic to monitor for signs of relapse. By measuring how often children who have recovered return for scheduled follow-up in the standard of care arm, we aim to understand gaps in care. Low adherence to the follow-up schedule may suggest that additional interventions are needed, or a reduced follow-up schedule should be considered if relapse rates are low.*Caregiver acceptability*. Caregivers complete quantitative surveys related to their experiences screening children for relapse in the screening arm, including data on ease of use, frequency of screening, whether the MUAC tape was lost or stolen, and evaluation of caregiver-perceived importance of screening and whether this is a priority for them in relation to other demands in their lives. A subset of 20 randomly selected caregivers will be invited to participate in an in-depth individual qualitative interview, focusing on their experience with malnutrition screening, diagnosis, treatment, and relapse as well as their child’s general health, and their experiences related to screening. Interviews will be conducted by a study investigator with expertise in qualitative methods. Interviews will be transcribed, translated into English, and analyzed based on an inductive and deductive approach to identify themes guided by immersion crystallization.*Clinic acceptability*. Acceptability from the clinic perspective will be assessed via in-depth interviews with nutritional program staff and clinic leadership. These interviews will focus on the evaluation of MUAC training, ease of implementation, and general barriers perceived by the clinic in the delivery of outpatient treatment for SAM. As part of these interviews, we will evaluate the resources that were required to implement the screening intervention and what is acceptable for implementation from the clinic perspective, including personnel time and space and privacy for training.

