
### Clinical outcomes

In addition to acceptability and feasibility endpoints, a number of clinical endpoints are measured at each follow-up time point. Although the trial is not powered to detect a meaningful difference in clinical endpoints, these data will provide important preliminary data for the design of a full-scale trial should feasibility criteria be met.*Proportion of children relapsing*. The proportion of children who relapse will be compared between study arms. Relapse to SAM will be defined as MUAC < 11.5 cm and/or WHZ < −3. Children who relapse to SAM will be re-admitted to the nutritional program. These children will continue to be monitored in the study. We will also assess the proportion of children who relapse to MAM by arm, defined as MUAC < 12.5 cm and/or WHZ < −2.*Time to detection of relapse*. Time from enrollment to first relapse will be analyzed in both arms. The date of relapse will be defined as the earliest date the relapse was identified in the clinic, via a planned study visit or unscheduled clinic visit.*Anthropometric outcomes*. At all study visits, weight, height, and MUAC measurements will be collected. We will compare growth based on weight and height as well as anthropometric measures defined by weight-for-age *Z*-score (WAZ), height-for-age *Z*-score (HAZ), and WHZ, calculated based on 2006 WHO child growth guidelines [9].*Vital status*. Vital status is assessed at the 6-month visit, and children are classified as alive, died, or unknown. Families who do not return to the clinic for the 6-month study visit will be contacted via phone call and/or home visit to ascertain vital status.*Hospitalization*. At each study visit, caregivers will be asked about any health care sought for the child since their previous visit. Reasons for seeking health care, and if the child was hospitalized overnight, will be recorded. In addition, data from the clinics in which children are enrolled are extracted from clinic records, and hospital records are queried, and data recorded for any hospitalizations of children enrolled in the study. To facilitate linking children to clinic and hospital records, a unique study identification number is placed in each child’s government-issued health card (*carnet de santé*). Clinic and hospital staff are sensitized to record this information for children enrolled in the trial.

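### Between enrollment and month 6, relapse and home screening are seen mainly in children who attend clinic, so a low relapse proportion alone cannot show that intervention is not needed

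*Protocol article*

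**What the plan says.** All references are to the protocol article.

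- **Use of the relapse proportion** (*Feasibility and acceptability outcomes*). It feeds the sample size and justification of a full-scale trial, and "A low probability of relapse would indicate that interventions intended to reduce the risk of relapse are not warranted". No numeric cut-off is given.
- **Interim visits** (*Participant timeline, procedures, and follow-up*). So that adherence to the schedule can be observed, "no efforts beyond those routinely implemented by the nutritional program to follow up children are employed". Measurement is tied to visits: "At each study visit, anthropometric measurements are collected".
- **Month 6.** The same section says "phone calls to find the family and home visits are used in case the caregiver does not return to the clinic". *Clinical outcomes* says that families who do not return "will be contacted via phone call and/or home visit to ascertain vital status". Neither section says that a home visit includes MUAC, weight and height.
- **Dating of relapse** (*Clinical outcomes*). "The date of relapse will be defined as the earliest date the relapse was identified in the clinic, via a planned study visit or unscheduled". The last word refers to unplanned attendances at the clinic.
- **Screening adherence** (*Feasibility and acceptability outcomes*). "Caregivers in the MUAC screening arm will be asked to report how often they screened their child at each follow-up visit". Infrequent screening is to be read as a sign that the intervention may not be acceptable or feasible. A caregiver survey also records screening frequency; its timing is not given.
- **Window.** *Feasibility and acceptability outcomes* describes the relapse proportion as covering six months after discharge. *Study design* says "Caregiver-child dyads are followed for 6 months from enrollment", and *Recruitment and eligibility criteria* allows recovery at any time in the month before.

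**The concern.** The Abstract gives the reason for the trial: attendance after recovery can be variable, and missed visits may delay the diagnosis of relapse. The relapse proportion is then obtained largely through those same visits. Where attendance is poor, some relapses begin and resolve, or end in death or loss, without being measured, and the observed proportion falls. The plan reads a low proportion as evidence that relapse is rare, with no stated allowance for unmeasured time. It also says that a reduced follow-up schedule could be considered where attendance is low and relapse rates are low, although low attendance can itself produce the low relapse figure.

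Screening adherence has a related weakness. A caregiver who misses a visit gives no report at that visit, and the least engaged caregivers are the likeliest to be absent.

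At stake are the justification for a full-scale trial and its sample size. Measurements not taken at month 6 cannot be recovered by analysis.

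**Working it through.** The plan has no figure to reproduce: the 200 dyads were chosen on logistical and resource grounds. The checks below are illustrations. Attendance, episode length, true relapse and screening rates are assumptions.

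**1. Relapse, all enrolled as denominator**

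Assume true 6-month relapse R = 20%, onset uniform over 26 weeks, visits every 26/6 = 4.33 weeks, attendance *a* at months 1-5, 85% measured at month 6 (the edge of the retention target), and no detection at unscheduled visits.

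Observed = R × average over onset times of the sum over later visits *k* of P(episode still present at *k*) × p_k × product of (1 − p_j) over earlier visits *j* since onset. Here p = *a* at months 1-5 and 0.85 at month 6.

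A case that can be checked by hand is a fixed 4-week episode, which meets at most one visit:

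- share of episodes meeting a visit: 4/4.33 = 0.923
- average chance of measurement at *a* = 0.4: (5 × 0.4 + 0.85)/6 = 0.475
- observed: 0.20 × 0.923 × 0.475 = 8.8%
- at *a* = 0.6: (5 × 0.6 + 0.85)/6 = 0.642, so 0.20 × 0.923 × 0.642 = 11.8%

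The same formula evaluated numerically, true value 20%:

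| Episode length | 40% attendance | 60% attendance |
|---|---|---|
| exponential, mean 4 weeks | 7.0% | 8.8% |
| exponential, mean 12 weeks | 12.3% | 14.0% |
| fixed 4 weeks | 8.8% | 11.8% |
| fixed 12 weeks | 16.3% | 18.2% |

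This gives about 7-16% and 9-18%. Two limits help in reading it.

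- Part of the shortfall comes from monthly spacing and not from missed visits. With every visit attended, the exponential 4-week case would still read 0.20 × (4/4.33) × (1 − exp(−4.33/4)) = 12.2%.
- If no episode resolves before month 6, the loss nearly vanishes. A relapse with onset in month *m* is missed with probability 0.15 × (1 − *a*)^(6−*m*). Averaged over *m* at *a* = 0.4 this is 0.15 × (1 + 0.6 + 0.36 + 0.216 + 0.130 + 0.078)/6 = 0.060, so observed = 0.20 × 0.940 = 18.8%.

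A separate monthly-step model took a true value of 10%, 85% measured at month 6, and a chance of 0.3 to 1.0 that an episode persists to the next visit. Observed relapse was 5.6-9.4% at 40% attendance, 7.1-9.6% at 60% and 8.5-9.7% at 80%. The 95% Wilson interval for 20/200 is 6.6-14.9%, so a reading of 5.6% lies outside sampling error around 10% and a reading of 8.5% does not.

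**2. Relapse, attenders as denominator**

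The sign is then not fixed. With a true point prevalence of 10%:

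- relapsed children attend less (40% against 70%): 0.10 × 0.4/(0.10 × 0.4 + 0.90 × 0.7) = 0.04/0.67 = 6.0%
- relapsed children attend more (70% against 40%): 0.07/(0.07 + 0.36) = 16.3%

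**3. Screening adherence**

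True = *a* × q_attend + (1 − *a*) × q_miss; reported = q_attend.

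- *a* = 0.6, q = 90% and 40%: true 0.6 × 0.9 + 0.4 × 0.4 = 70%, reported 90%.
- *a* = 0.4, q_attend = 80%, q_miss from 20% to 80%: true 44% to 80%, reported 80%.
- *a* = 0.4, q_attend = 80%, q_miss = 90%: true 0.4 × 0.8 + 0.6 × 0.9 = 86%, so the reported 80% is too low.
- Unreported weeks counted as unscreened, first case: 0.6 × 0.9 = 54%, which is 16 points below the assumed truth, where the reported figure is 20 points above it.

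**4. Window**

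A child enrolled one month after recovery is observed from month 1 to month 7 after discharge. A relapse in the gap lies outside the observed period.

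**The case against.** The strongest reply is that ascertainment is wider than scheduled attendance. Unscheduled clinic visits count, and month 6 is traced with a retention target above 85%. At each visit caregivers report care sought since the previous one. Clinic records are extracted and linked by study number, although the article describes this under hospitalization. Interim tracing is withheld for a good reason, since attendance is itself an outcome. All of this stands, and it is why the wording here is *mainly* and *probably*. It does not close the gap. Month-6 tracing can find only relapse still present, its stated aim for non-returners is vital status, and a phone call yields no MUAC or WHZ.

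Three stronger readings are tempting, and the article does not support them.

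- A reader might infer that an unseen child is counted as not relapsed. No denominator or rule for missed visits is stated, and an article may leave that to the full protocol or analysis plan.
- A reader might infer that a low relapse figure would formally stop the program. Numeric success criteria cover only enrollment, refusal and retention, and low attendance is itself read as a possible reason for additional interventions.
- A reader might infer that adherence is certainly biased upward. That needs non-attenders to screen less, and the caregiver survey and month-6 reports may recover part of the loss.

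It can also be said that 4-12 week episodes are assumed, and that longer untreated episodes would shrink the shortfall. That is right; the size is open.

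**Conclusion.** The point holds in a limited form. Followed as written, poor interim attendance can produce a falsely low relapse proportion, and the article ties a low proportion directly to a conclusion of no need. The downward direction for relapse rests on all enrolled children being the denominator. The upward direction for adherence rests on non-attenders screening less. The shortfall could be large (a true 20% reading as 7%) or slight (reading as 18% or more), depending on attendance, episode length, coverage at month 6 and detection at unscheduled visits. The article fixes only a coverage target for month 6 and none of the others. The mismatch between a post-discharge label and observation from enrollment is plain on the page and needs no model.

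**What to change.** 1. State the relapse proportion as over 6 months from enrollment, and report the distribution of the discharge-to-enrollment gap.
2. At traced month-6 home visits, take MUAC, weight and height. At every month-6 contact, including phone calls, ask about re-admission for malnutrition and about screening frequency over the whole period.
3. Count SAM re-admissions found in the clinic records and program registers already in use.
4. Report relapse with bounds for child-months without a measurement. The lower bound counts detected relapses only; the upper applies a relapse rate, fixed in advance, to unmeasured child-months. Conclude that interventions are not needed only if the upper bound or upper confidence limit is also low.
5. Report screening adherence both among reported weeks and over all randomized screening-arm child-weeks, as a range (54% to 90% in the first adherence example). Do not make the version that counts unreported weeks as unscreened the main figure.

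A full interval-censored model with delayed entry is not required. Interim non-tracing stays, so the attendance outcome is preserved. The cost is a few added items at an existing contact, a wider relapse interval and a less favorable adherence range. Recruitment began on 1 December 2023, so the first month-6 visits fall around June 2024, after the article's status date of 31 January 2024. At that date the month-6 additions could still have reached every child.

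### The relapse proportion used to judge need and visit schedule falls when attendance falls, so a low value with poor attendance cannot support either conclusion

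*Protocol article*

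**What the plan says.** In Feasibility and acceptability outcomes, the adherence item gives two possible readings of poor attendance in the standard-of-care arm. The first is that additional interventions are needed. The second is that "a reduced follow-up schedule should be considered if relapse rates are low". The relapse item in the same section states: "A low probability of relapse would indicate that interventions intended to reduce the risk of relapse are not warranted". It also makes the relapse proportion an input to the sample size and justification of a full-scale trial.

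Three other statements fix how relapse comes to be observed:

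- Clinical outcomes defines relapse by measured MUAC and/or WHZ. Its dating sentence, which goes on to name unplanned attendance, reads in the main: "The date of relapse will be defined as the earliest date the relapse was identified in the clinic, via a planned study visit or unscheduled".
- Participant timeline, procedures, and follow-up says of the monthly visits: "To understand adherence to the follow-up schedule, no efforts beyond those routinely implemented by the nutritional program to follow up children are employed".
- For month 6 the same section is different: "phone calls to find the family and home visits are used in case the caregiver does not return to the clinic". Under Vital status, Clinical outcomes says that families who miss the month-6 visit "will be contacted via phone call and/or home visit to ascertain vital status".

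**The concern.** The relapse figure is used to choose between two opposite readings of low adherence, yet it depends on adherence itself. A child who relapses in month 2, misses the next visits and is back above the thresholds by month 6 counts as not relapsed. So does a child who relapses and is then lost. The fewer visits are kept, the more such children there are, and the more the data appear to favour fewer visits.

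The relapse item has the same weakness in firmer words, since low relapse would indicate no need for intervention. The error runs in one direction, towards no need, and is largest where surveillance is weakest. The Abstract itself says that missed visits may delay the diagnosis of relapse. The issue concerns the absolute burden figure and what is concluded from it, and arises even without any difference between arms.

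**Working it through.** The article gives no expected relapse, attendance or relapse duration, and the sample size of 200 is logistical. There is thus no figure of the plan's to reproduce, and the check is an illustration on stated assumptions.

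**Inputs from the article.** Monthly follow-up for 6 months; no extra tracing at months 1 to 5; tracing at month 6; retention target above 85%.

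**Assumptions.** True 6-month relapse p = 20%, at a constant hazard. Each of visits 1 to 5 is attended independently with probability a. Relapse status is measured at month 6 in a share m of children: 85%, or 0% as an extreme bound. Relapse lasts one month on average, two months on average, or until seen. Observed relapse is the share of all enrolled children who are measured while relapsed.

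**Step 1: persistent relapse, by formula.** Let s = 0.80^(1/6) = 0.9635. The probability of relapsing in month k is w_k = s^(k−1)(1 − s), which gives 0.0365, 0.0352, 0.0339, 0.0327, 0.0315 and 0.0303 (sum 0.200). Such a relapse is missed with probability (1 − a)^(6−k)(1 − m).

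- For a = 0.3, the sum of w_k × 0.7^(6−k) is 0.0945.
- With m = 0.85, observed = 0.200 − 0.15 × 0.0945 = 0.186.
- With m = 0, observed = 0.200 − 0.0945 = 0.1055.

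For a = 0.9, the corresponding sum is 0.0338. Observed relapse is then 0.200 − 0.15 × 0.0338 = 0.195, or 0.200 − 0.0338 = 0.166.

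**Step 2: all durations, by simulation (400,000 children per cell).** Observed relapse, true value 20%, no unscheduled detection:

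| Month-6 status | Relapse duration | a = 90% | a = 50% | a = 30% |
|---|---|---|---|---|
| 85% measured | mean 1 month | 11.6% | 8.3% | 6.3% |
| 85% measured | mean 2 months | 14.7% | 11.7% | 9.6% |
| 85% measured | persistent | 19.5% | 19.1% | 18.6% |
| none measured | mean 1 month | 10.0% | 6.3% | 4.0% |
| none measured | mean 2 months | 12.6% | 8.8% | 5.9% |
| none measured | persistent | 16.6% | 13.8% | 10.6% |

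The persistent rows agree with step 1 to rounding and simulation error. Observed relapse also falls with attendance when true relapse is set to 10% or 37%.

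**Step 3: unscheduled visits.** If 30% of relapses are also found at unscheduled visits (assumed), the first row becomes 14.1% at 90% attendance and 10.3% at 30%. The drop shrinks from 11.6 − 6.3 = 5.3 points to 14.1 − 10.3 = 3.8 points.

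**Step 4: is relapses per attended visit a way out?** No. Take true relapse 15%, month 6 seen in 85% and relapse persisting until seen. Simulated observed relapse is 14.6% at 90% attendance and 13.2% at 10%. Expected attended visits per child are 5 × 0.9 + 0.85 = 5.35 and 5 × 0.1 + 0.85 = 1.35. The ratio rises from 0.146/5.35 = 0.027 to 0.132/1.35 = 0.098 with the truth unchanged. If 40% of undetected episodes resolve each month, it still rises, from 0.141/5.35 = 0.026 to 0.065/1.35 = 0.048.

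**The case against.** A reader might infer that the plan contains a self-confirming rule: relapse is seen only at kept appointments, so low adherence by itself generates low relapse, and the trial then recommends fewer visits. The documents do not support that, for three reasons.

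- **There is no rule.** The adherence item speaks of what low adherence may suggest and what should be considered. It names additional interventions first and sets no threshold. The Discussion says that the trial does not evaluate a reduced schedule and leaves that to possible future studies.
- **Scheduled visits are not the only route to detection.** Unscheduled clinic visits count, and families absent at month 6 are traced. A relapse still present at month 6 can be found whatever the earlier attendance, provided the traced child is measured.
- **Low attendance lowers the figure but need not make it low.** With persistent relapse and 85% measured at month 6, the loss between 90% and 30% attendance is 0.9 points. The large losses need relapses that resolve unseen, or traced children who are not measured.

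It can also be said that denominators and tabulations belong in an analysis plan or results paper.

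The first three points stand and limit the claim. They do not remove it. The sentence on interventions being unwarranted is less hedged, and nothing shown conditions either reading on attendance. Credit for month-6 tracing is also uncertain: a phone call yields no MUAC or WHZ, and the outcomes section gives the purpose of the contact as vital status. Elsewhere anthropometry is tied to each study visit, so whether home visits include it is open. Finally, the point is about an inference the article states, not about detail it leaves out.

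**Conclusion.** The concern holds in limited form. Relapse per enrolled child depends on attendance between enrolment and month 6, and lower attendance always moves it downwards. Under the assumptions above, going from 90% to 30% attendance costs between 0.9 points (persistent relapse, 85% measured at month 6) and 6.7 points (mean duration two months, none measured at month 6: 12.6 − 5.9), against a true 20%. In the short-relapse case with 85% measured, the figure is roughly halved, from 11.6% to 6.3%. Where between these the trial will fall cannot be told from the documents.

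Low observed relapse together with low interim attendance is therefore uninformative about need or schedule. Low observed relapse with high attendance and high month-6 measurement is much less affected by missed visits.

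**What to change.** **Wording, in Feasibility and acceptability outcomes.** State that relapse per enrolled child is a lower bound. State that neither the reduced-schedule reading nor the not-warranted reading will be drawn from it when interim attendance is low, and say beforehand what counts as low.

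**Reporting.**

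1. Relapse alongside the number of children measured at each visit.
2. Relapse status at month 6 among children with known status, including any traced children who are measured, with bounds that count the unmeasured as all relapsed or none relapsed. This is prevalence at month 6, so it complements the cumulative figure and does not replace it.
3. In the standard-of-care arm, the share of SAM relapses first found after a missed visit or only at month 6.

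Do not use relapses per attended visit as an attendance-free measure, because it rises as attendance falls.

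**Cost.** Two extra tables from data already collected, and a more cautious conclusion. The bounds may be wide: with 85% of 200 measured, 30 children are unknown and the bounds span 30/200 = 15 percentage points.
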